### 2.10. Material Used for Smoking Determination and Other Instruments

A CO-oximeter of the brand “Co Check”, sold by MD Diagnostics Ltd. (Kent, UK), distributed by Sibel S.A. (Barcelona, Spain), code 01PLS18B, with a sensitivity of 1 ppm and an accuracy (repeatability of 2%, purchased in 2023) will be used to measure smoking and smoking cessation. To differentiate between smokers and ex-smokers, the criteria established in the Andalusian Comprehensive Smoking Plan (ACSP) will be followed [24].

Regarding arterial pressure, an OMROM M6-Confort (HEM-7000-E-V) (Omron HealthCare, Kyoto, Japan) will be used for the blood pressure measurement. The height and weight (Barys Plus Ref ASI06472; Asimed, Sibel group, Barcelona, Spain) of the participants will be recorded.

### 2.11. Intervention

Interventions will be developed by a multidisciplinary team with experience in tackling tobacco consumption. Physical exercise recommendations will be made by specialists in Medicine, Physical Education, and Sport Sciences and will be carried out in line with the Andalusian Physical Exercise Prescription Plan (APEPP) [1], the recently published regional plan for Andalusia. Therefore, this study consists of two treatment arms:A.Smokers who are going to be prescribed targeted physical exercise and brief advice to stop smoking while receiving cytisinicline treatment (1.5 mg tablets) according to the care process: EXPERIMENTAL ARM.B.Smokers who will receive a standard leaflet explaining physical exercise to the general population and brief advice on smoking cessation when starting cytisinicline treatment, according to the care process: CONTROL ARM.

#### 2.11.1. Prescription of Targeted Physical Exercise

The baseline level of physical activity and physical exercise will be determined using the modified version of the Global Physical Activity Questionnaire (GPAQ) [22] which will be administered to participants in the experimental arm. In this regard, study participants will be classified according to low (inactive), moderate, and high levels of physical activity following the criteria of the GPAQ [22].

For the prescription of targeted physical exercise, the guidelines established by the American College of Sports Medicine (ACSM) [2], those indicated in the “Guide for professionals” of physical activity recommendations and prescription of physical exercise for health” recently published by the Andalusian Regional Government [25], and those suggested in the Stockton review [16] will be followed.

A combined aerobic and strength exercise, and Flexibility or Range of Motion and Neuromotor Capabilities protocol will be implemented, designed to promote adherence and supervised through continuous monitoring. Participants will engage in moderate-intensity aerobic exercise for a minimum of 30 min on alternate days, complemented by strength exercises targeting the major muscle groups. Exercise intensity will be monitored using beats per minute, either manually or by means of smartwatch-type devices in line with the “ACTIVITAL” platform recently implemented by the Andalusian Regional Government [26].

A standard leaflet with basic physical exercise recommendations will be provided at the start of the prescription (Table 1, Table 2 and Table 3). In addition, inactivity or physical activity habits (such as walking to work), as well as regular physical exercise and sports activities will be collected at the initial interview in order to include the smoker in the appropriate arm of the study.

To achieve individualisation and progression, a multi-level system (low, moderate, and high) has been implemented (Table 1, Table 2 and Table 3). Participants will be assigned to an initial level based on their GPAQ results and individualised follow-up assessments at each visit. This system allows progression to higher levels as their physical condition improves. For example, a participant may progress from low to moderate level over time, but this advancement may vary across exercise categories. For instance, while cardiorespiratory exercises may progress to a higher level, strength exercises might remain at the initial level.

To clarify this structure, exercise types within each level have been specifically labelled (e.g., Low Level 1.1 for Cardiorespiratory Endurance, Low Level 1.2 for Muscle Strength and Endurance, etc.) and are detailed in (Table 1, Table 2 and Table 3).

The prescription includes explicit descriptions of the exercises, intensities, and progression criteria, ensuring replicability. The load progression will follow predefined criteria, considering physical responses, including improvements in the number of repetitions, sets, session durations, and intensity levels (e.g., %HR max or %1RM). Adjustments will be made based on participant feedback and performance, ensuring gradual and safe increases in load. The physical exercise prescribed shall be individualised and adapted to the person’s physical condition, motivating and facilitating social relations and non-detrimental. The principles of progression and alternation shall also be respected. The exercise will be progressive depending on the volume and intensity applied to each person according to their physical condition and supervised by experts in the field. If a participant has an injury or discomfort that prevents them from performing any of the proposed exercises, an alternative will be offered to achieve the same type of work.

Directed physical exercise will be recorded in an Electronic Data Collection Notebook (CRDe) and in the digital medical record using DIRAYA. To encourage adherence, a continuous, standardised and motivating follow-up will be carried out by video call or telephone call. Only study investigators will have access to this CRDe. In addition, this system has a mechanism of roles and profiles that allows each researcher to be assigned what information they can access, so it can be individualised.

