#### 2.11.2. Brief Advice

The brief advice will be consensual and provided by Family and Community Medicine specialists. It will be carried out in line with the guidelines established in the comprehensive plan against smoking in Andalusia, the integral smoking plan (PITA) [24]. Advice should be brief, opportunistic, personalised and clear (recommendation A). The strategy of this advice follows the mnemonic rule of the “5 As” (in Spanish): find out, advise, appreciate, help, and agree, the appropriate follow-up plan depending on the assigned arm, taking into account that the smokers participating in this study should be in the determination-action phase of the stages of change [10].

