### 2.14. Bias Control

Selection bias will be controlled by applying the same selection criteria to the participants in the different groups to be compared, which will have identical monitoring. In addition, in the collection of information, a record of losses to follow-up will be kept, collecting as much information as possible about them. Regarding misclassification bias, smoking will be considered as a criterion of truth, the measurement of 6 or more ppm of CO in exhaled air by CO-oximetry. Finally, multivariate analysis using logistic regression will control for various confounding factors.

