Gender inequalities may also influence access to and adherence to the resources needed to quit smoking. Women may face additional barriers, such as lower income, caregiving responsibilities and social stigma, which make it difficult for them to access smoking cessation programmes [33]. As mentioned above, one way to address these barriers is the use of a drug that is currently funded by the NHS, which facilitates access for people with fewer financial resources. On the other hand, the prescription of targeted physical exercise is intended to ensure a close follow-up of patients, which would encourage adherence to these programmes among this group of smokers. Integrating a gender perspective in this type of research contributes to a more inclusive science and the promotion of public health in an equitable manner.

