## 4. Discussion

To date, there are no studies comparing the efficacy of prescribing physical exercise as an adjunctive treatment to cytisinicline and brief advice to achieve smoking cessation, which is the aim of this research protocol.

Physical exercise per se can activate the dopamine reward system, facilitating the reduction of craving and withdrawal symptoms [34]. Recent studies show a relationship between positive and negative effects and craving. Kunicki et al. [7] suggest that a negative effect is associated with craving, which can be mitigated by exercise, finding greater reductions in craving in smokers who engaged in physical exercise. However, Stockton et al. indicate in their clinical trial that physical exercise does not improve smoking cessation, compared to so-called “wellness counselling”, although they draw attention to the importance of “individualisation” [16].

Regarding the role of physical exercise as an adjunctive treatment, some authors have investigated the synergy with medication against smoking. Thus, regarding the efficacy effects of physical exercise programmes combined with nicotine replacement therapy (NRT), Chen et al. [34] show in their systematic review of clinical trials moderate-high quality evidence that physical exercise can help NRT in short-term smoking cessation [24], suggesting future trials that include larger sample sizes, as well as strategies to increase adherence to exercise in the long term.

We know that NRT is one of the smoking cessation therapies that use classic so-called “first-line” drugs, the other first-line drugs being varenicline and bupropion. Both cytisinicline and varenicline are drugs specifically designed to aid smoking cessation, although the latter has been temporarily withdrawn from the market in Spain, unlike bupropion, which was initially designed as an antidepressant drug. The literature reviewed includes cytisinicline among the second-line smoking cessation drugs.

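### The protocol claims identical monitoring of the arms, but the experimental arm is given extra follow-up contact, so the contrast is exercise prescription plus that contact versus a leaflet

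*Protocol article*

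**What the plan says.** All references are to the protocol article.

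- Section 2.14 (Bias Control) describes its safeguard against selection bias as "applying the same selection criteria to the participants in the different groups to be compared, which will have identical monitoring".
- Section 2.12 gives one schedule of visits, from Day 0 to Day 365, for all participants. Visit 1 is by telephone and the others are face to face.
- Section 2.11.1 describes the exercise programme. It is supervised through continuous monitoring, and a baseline activity questionnaire (GPAQ) is administered to the experimental arm. The section adds: "To encourage adherence, a continuous, standardised and motivating follow-up will be carried out by video call or telephone call".
- Section 2.11.2 describes brief advice, which both arms receive. Its last step is to agree "the appropriate follow-up plan depending on the assigned arm".
- Section 2.23 (Gender Perspective) states that "the prescription of targeted physical exercise is intended to ensure a close follow-up of patients".
- Section 2.11 gives the control arm a standard exercise leaflet, brief advice and the drug. No section describes motivating calls or exercise supervision for this arm.
- Section 3 will read the result as the efficacy of prescribing exercise as an add-on. The abstract and sections 1 and 5 speak of a synergistic effect of the combination.

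**The concern.** Section 2.14 offers identical monitoring as a safeguard, but the design described elsewhere does not provide it. In a cessation trial, contact and encouragement may themselves affect quitting. If one arm gets more of them by design, a difference in quit rates cannot be credited to exercise.

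The analysis in section 2.13 cannot repair this. Intention-to-treat keeps the randomised groups intact, but those groups differ in contact as well as in exercise. Regression on potential confounders can adjust for characteristics that vary within an arm. It cannot separate exercise from contact when both are assigned together. At stake is what the trial may conclude, and whether a reader is wrongly assured that the arms differ in exercise only.

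**Working it through.** No figure in the plan belongs to this point, so the check sets the texts side by side.

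**Step 1: what is common to both arms.** Section 2.12 applies the visits on Days 0, 7, 30, 60, 90, 180 and 365 to every participant. Section 2.11 gives both arms cytisinicline and brief advice.

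**Step 2: what is not shown to be common.**

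- *Supervision.* Section 2.11.1 places continuous monitoring, reassessment and progression through levels inside the exercise programme. Control has a leaflet and nothing to supervise.
- *Questionnaire.* Section 2.11.1 says the baseline GPAQ is administered to the experimental arm. Section 2.9 lists the GPAQ among the explanatory variables without naming an arm, so the two sections need to be aligned.
- *Calls.* They sit in the exercise section and their stated purpose is adherence. That they go to the experimental arm only is an inference from placement and purpose. Section 2.23 supports it, and no section gives the calls to controls.
- *Follow-up plan after brief advice.* Section 2.11.2 makes it depend on the arm and does not confine the difference to exercise.

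**Step 3: compare with the claim.** Section 2.14 states identical monitoring without qualification. Step 1 supports that for scheduled visits only, and Step 2 contradicts it for the rest.

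**Step 4: what the contrast identifies.** Write the true difference in 12-month quit rates as

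D = e + c + i,

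where e is the effect of exercise, c the effect of the added contact, and i any interplay between them. Both are switched on together in one arm and off together in the other. Two arms yield one contrast, which estimates D. They do not yield e. Every experimental participant is offered both and no control is offered either, so no covariate adjustment separates them.

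**Step 5: synergy with the drug.** Synergy means that the combination does more than its parts would add up to. Both arms receive cytisinicline and brief advice, so the effect of the exercise package without the drug is never observed. The design can show whether the package adds to drug and advice. It cannot show synergy.

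**Step 6: size.** The documents give no value for c. The only yardsticks are in section 2.3: a pooled difference of 3.18 percentage points and a delta of 5 points. These show what any contact effect would be measured against, but they do not say how large it is.

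**The case against.** The best defence is that this is a legitimate pragmatic comparison. Adherence follow-up is described inside the prescription, section 2.23 openly says the prescription is meant to bring close follow-up, and section 3 speaks of prescribing exercise, not of exercise as such. This stands in part: a package comparison needs no attention control, and none is asked for here. But the synergy wording and the monitoring claim go further than a package comparison allows.

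A second defence is that identical monitoring means only the common visits of section 2.12. That reading is reasonable, and if it is the intended one, a short change of wording settles it. As written, the sentence has no such limit.

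Third, the calls may not be extra or may not be confined to one arm. Their number is not given, Visit 1 is a telephone visit for everyone, and the limitations section mentions telephone follow-up to reduce losses. The point is therefore stated as an inference, and the remedy includes saying who gets the calls. Fourth, an arm-dependent plan may mean only that one arm has exercise to follow up. That is plausible, but the text leaves cessation follow-up free to differ as well.

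Three stronger readings are tempting, and the documents do not support them:

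- *Brief advice is timed differently by arm.* Section 2.11 has "brief advice to stop smoking while receiving cytisinicline treatment (1.5 mg tablets) according to the care process: EXPERIMENTAL ARM" against "brief advice on smoking cessation when starting cytisinicline treatment, according to the care process: CONTROL ARM". Both refer to the same care process, and section 2.11.2 sets one advice procedure, so this may be loose drafting.
- *Better attendance in the contacted arm mechanically inflates its quit rate.* That needs a rule counting unverified participants as smokers. The article states no such rule, and section 2.13 says missing data will not be imputed. Attendance related to outcome could still bias an analysis of those observed, but its direction and size cannot be derived from the text.
- *The trial cited in section 4 proves the point.* Its authors "indicate in their clinical trial that physical exercise does not improve smoking cessation" compared with wellness counselling. That result says nothing about a contact effect in the present trial.

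**Conclusion.** The point holds in a limited form and should be corrected. Section 2.14 claims a bias-control property that the described design has only for the scheduled visits. A difference in cessation will identify the exercise prescription with its follow-up contact versus a leaflet, on top of drug and brief advice. It will not identify exercise alone or a synergy.

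The size of the contact effect is unknown. Any percentage of the 3.18-point planning difference would merely rescale an assumed effect, so none is offered. The trial remains interpretable as a package comparison.

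The conclusion rests on one inference, that the motivating calls go to the experimental arm only. If controls also receive them, that strand falls. The supervision and the arm-dependent follow-up plan would still need to be reconciled with section 2.14.

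**What to change.** 1. In section 2.14, replace the claim of identical monitoring with *identical scheduled assessment visits*. In section 2.11.1, say which arm receives the video or telephone calls.
2. In section 2.11.2, keep the cessation content of brief advice and its cessation follow-up the same in both arms, so that the arm-dependent part covers exercise follow-up only. Limit the section 2.11.1 calls to exercise content.
3. In sections 2.13, 3 and 5, state the contrast as *exercise prescription with its follow-up contact versus leaflet*, and drop or qualify the synergy wording there. Report the number of study contacts and Visit 6 attendance by arm beside the quit rates.

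These steps do not equalise contact. They keep cessation support constant, make the remaining difference visible and match the claim to the design. The cost is changed wording, a small burden of recording contacts in both arms, and a narrower conclusion. No extra visits or attention control are needed. Contacts should be recorded as they occur, because they would be hard to recover later.

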## 1. Introduction

Increasing importance is being given to the so-called “physical exercise prescription”. Proof of this is the recent specific plan implemented in Andalusia, Spain [1]. Current scientific evidence shows the relationship between good physical fitness and reduced incidence of certain chronic diseases, ranging from “some evidence of reduced disease rates in the case of lung disease (with few studies conducted)” to “good evidence” for hypertension and “excellent evidence” for reduced disease rates in obesity, coronary heart disease and all-cause mortality [2,3].

Smoking can be considered a chronic, addictive disease with a tendency to relapse. It has associated comorbidity, such as multiple cancerous processes, chronic obstructive pulmonary disease, and other pathologies that also constitute important cardiovascular risk factors, such as hypertension and obesity [4,5]. In this respect, obesity is a common barrier that smokers, especially women, often cite as a reason for delaying quit attempts. It is therefore interesting to consider adjuvant therapy that also helps to control risk factors, such as the prescription of physical exercise, in people who decide to quit smoking. This may also be useful for dealing with the withdrawal syndrome caused by smoking cessation. In this regard, a meta-analysis published in 2023 indicates that short interventions with physical exercise are effective in reducing craving and withdrawal symptoms in smokers, as well as helping to improve their mood [6]. In the same vein, a clinical trial to test the efficacy of a 12-week exercise intervention in conjunction with health education interventions also shows greater reductions in craving while attenuating the negative emotional effect that is generally associated with craving [7]. Cytisinicline is a recently financed drug by the Spanish Health System to help quit smoking, increasing the demand to cope with this addiction [8,9,10]. In this sense, the aim of this protocol is to evaluate the efficacy of the synergistic effect of the combination of targeted physical exercise, together with brief advice and taking the drug cytisinicline, to achieve smoking cessation.

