## 2. Materials and Methods

### 2.1. Study Design

A multicentre, randomised and controlled experimental study with two parallel branches, to be carried out by a multidisciplinary team of different specialties (medicine, pharmacology and physical education sciences) of the Maimonides Institute of Biomedical Research of Cordoba (IMIBIC), in the field of the Andalusian Public Health System (APHS), is proposed.

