### 2.12. Participant Chronology and Schedule of Visits

All participating smokers will be followed up, either in person or by telephone, according to the plan established in this study and at the visits indicated below (Figure 1):-Selection visit (Day 0): FACE-TO-FACE. The potential participant is proposed to participate in the study. A check is made to ensure that the patient has no medical or other history that might contraindicate the prescription of physical exercise. The patient receives the information and signs the informed consent form if he/she wishes to be included in the study.-Visit 0 (Day 0): FACE-TO-FACE. Baseline data are collected on the previously mentioned variables. The necessary criteria for prescription are completed. The drug is prescribed to be approved within 24h, and a treatment start date is set.-Visit 1 (Day 7 ± 2): TELEPHONE. Data are collected, and the participant is asked if there are any problems with the motivation to continue.-Visit 2 (Day 30 ± 4): FACE-TO-FACE. Data are collected, and questions are asked if there have been any problems with the physical exercise, motivating for its continuation.-Visit 3 (Day 60 ± 7): FACE-TO-FACE. Data are collected, and questions are asked if there have been any problems with the physical exercise, motivating for its continuation.-Visit 4 (Day 90 ± 7): FACE-TO-FACE. Data are collected, and a question is asked as to whether there have been any problems with the physical exercise, motivating the patient to continue.-Visit 5 (Day 180 ± 15): FACE-TO-FACE. Data are collected, and a question is asked as to whether there have been any problems with the physical exercise, motivating the patient to continue.-Visit 6 (Day 365 ± 30): FACE-TO-FACE. Data are collected.

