## 5. Conclusions

In conclusion, this study protocol (NCT06579846) aims to evaluate the efficacy of the synergistic effect of the combination of prescribed targeted physical exercise as an adjuvant therapy, together with brief advice and taking the drug cytisinicline to achieve smoking cessation in 18 to 65 years old smokers, through a multicentre, randomised and controlled experimental study with two parallel branches, to be performed by a multidisciplinary team, in primary care. The protocol provides specific interventions to achieve individualisation and progression, a multi-level system (low, moderate, and high) that could favour good physical fitness as well as reduced incidence of inactivity and certain chronic smoking-associated comorbidity, such as multiple cancerous processes, chronic obstructive pulmonary disease, and other pathologies that also constitute important cardiovascular risk factors, likes hypertension, weight gain and obesity, which are usually a common barrier to quit smoking, especially for women.

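### A two-arm trial with cytisinicline and brief advice in both arms can estimate the add-on effect of an exercise package but not synergy, and the claim of identical monitoring holds only for the shared visits

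*Protocol article*

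**What the plan says.** **Aim.** The Introduction states that "the aim of this protocol is to evaluate the efficacy of the synergistic effect of the combination of targeted physical exercise", with the drug and brief advice as the other two components. The Abstract gives the same aim, and section 5 (Conclusions) says that the protocol "aims to evaluate the efficacy of the synergistic effect of the combination of prescribed targeted physical exercise as an adjuvant therapy".

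**Design.** Section 2.1 describes "A multicentre, randomised and controlled experimental study with two parallel branches". Under section 2.11 the experimental arm is to be "prescribed targeted physical exercise and brief advice to stop smoking while receiving cytisinicline treatment (1.5 mg tablets) according to the care process". The control arm has the same drug and the same kind of advice, with a general exercise leaflet in place of the prescription.

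**A second wording of the aim.** Section 3 (Expected Results) treats exercise as an adjuvant to standard multicomponent treatment. Section 4 (Discussion) names exercise as an adjunct to cytisinicline and advice, and calls that the aim.

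**Follow-up.** Section 2.14 says that selection bias will be controlled by applying the same selection criteria to "the different groups to be compared, which will have identical monitoring". Section 2.11.1, on the exercise prescription, says that to support adherence "a continuous, standardised and motivating follow-up will be carried out by video call or telephone call". Section 2.11.2 ends the brief advice with agreement on "the appropriate follow-up plan depending on the assigned arm".

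**Visits.** Section 2.12 opens with one schedule for all participants. At Visits 2 and 3 "questions are asked if there have been any problems with the physical exercise, motivating for its continuation", and Visits 4 and 5 say the same in nearly the same words. No arm is named.

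**The concern.** The aim determines what the trial may conclude. If it is to show synergy, a difference between the arms will be read as evidence that exercise and cytisinicline work better together than their separate effects would predict. The design contains no comparison that bears on that.

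The monitoring claim matters for attribution. If the groups really were followed identically, a difference could be credited to exercise. If the exercise arm also has more frequent and more motivating contact, the difference belongs to exercise and contact together. The visit text raises the opposite worry: encouragement to exercise given to controls as well would narrow the contrast between the arms.

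**Working it through.** No figure in the plan decides this point, so the check concerns what the design can identify and whether the sections agree.

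**1. What synergy requires.** Let p(E,C) be the 12-month quit rate with exercise package E (1 or 0) and cytisinicline C (1 or 0), everyone having brief advice.

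| | Cytisinicline | No cytisinicline |
|---|---|---|
| Exercise package | p(1,1): experimental arm | p(1,0): no arm |
| No exercise package | p(0,1): control arm | p(0,0): no arm |

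On the risk-difference scale:

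synergy = [p(1,1) − p(0,1)] − [p(1,0) − p(0,0)]

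The trial observes the first bracket only. Write the second, unobserved bracket as D0. As an illustration only, let the first bracket equal the pooled difference in section 2.3, 3.18 points:

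- D0 = 0: synergy = 3.18 − 0 = +3.18 points
- D0 = 3.18: synergy = 3.18 − 3.18 = 0
- D0 = 5 (the delta in section 2.3): synergy = 3.18 − 5 = −1.82 points

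The same trial data fit synergy, simple additivity and antagonism. Neither 75 nor 289 per arm changes this, because more participants sharpen only the first bracket. Moving to the odds-ratio scale of the logistic regression in section 2.13 does not help: cytisinicline is constant across participants, so an exercise-by-drug term cannot be separated from the exercise term. Synergy with brief advice fails for the same reason, since both arms receive it.

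**2. What the sections say about follow-up.**

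| Section | Content | Same in both arms? |
|---|---|---|
| 2.14 | Groups monitored identically | Claimed |
| 2.12 | Common scheduled visits, including a telephone visit at day 7 | Yes |
| 2.11.1 | Exercise supervised by continuous monitoring | Part of the exercise protocol |
| 2.11.1 | Motivating video or telephone follow-up, for adherence | Described only under the exercise prescription |
| 2.11.1 | GPAQ administered | Experimental arm named |
| 2.11.2 | Follow-up plan agreed | Depends on arm |
| 2.23 | Exercise prescription intended to bring close follow-up | Tied to the exercise prescription |

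The schedule in section 2.12 lists no video calls and no continuous calls, so the contact in section 2.11.1 appears to be additional. On the GPAQ, section 2.9 lists it as a study variable without restriction by arm, so that entry is itself unclear.

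**3. What the observed contrast contains.**

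p(1,1) − p(0,1) = effect of exercise and its supportive contact, less any effect of exercise encouragement given to controls

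One contrast cannot be split into its components. Taken whole, it is still a valid randomised comparison of the package with the control treatment.

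**4. The visit wording.** Section 2.12 applies the visits to everyone and does not limit the exercise encouragement to one arm. It speaks of continuing the exercise, however, and section 2.11 prescribes exercise only in the experimental arm. The text permits both readings.

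**The case against.** The strongest reply is that the design and analysis already fit the add-on question. Sections 3 and 4 word it that way, section 5 uses the adjuvant wording in the same sentence as the synergy wording, section 4 uses synergy loosely for exercise added to nicotine replacement, and section 2.13 plans an ordinary intervention-effect regression with no interaction test. On this view one adjective is wrong. This stands in part: the trial is sound for the add-on question. But the adjective sits in the aim as given in the Abstract, Introduction and Conclusions, where readers will look for what a positive result means.

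On monitoring, no sentence says that controls receive no calls. The Limitations section mentions telephone follow-up generally, as a measure against losses. The claim in section 2.14 stands beside equal selection criteria and may mean the common schedule. The arm-dependent plan in section 2.11.2 may mean no more than exercise versus leaflet. Adherence contact is also a natural part of an exercise prescription, and comparing a whole package with usual care is legitimate. All of this stands, and it limits the point to the scope of the claim. Section 2.14 does not restrict itself to scheduled visits, and sections 2.11.1 and 2.23 indicate closer contact with the exercise prescription.

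On Visits 2 to 5, encouraging continuation most naturally refers to prescribed exercise, and the flowchart cited there is not available in the text reviewed. What remains is an ambiguity.

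**Conclusion.** The stated aim of evaluating synergy cannot be met with these two arms at any sample size. This follows from the arm definitions alone and needs no assumption about quit rates. The trial identifies the add-on effect of the exercise-prescription package in smokers receiving cytisinicline and brief advice.

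The claim of identical monitoring is supported only for the common visit schedule. That finding rests on an inference, from where the motivating calls are described, their adherence purpose, and sections 2.11.2 and 2.23, that the extra contact accompanies the exercise prescription.

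A reader might infer more than the article supports:

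- **That controls certainly receive no motivating calls.** This is not stated.
- **That any conclusion would be wrong.** The package effect is validly estimable.
- **That the plan promotes exercise to controls at four visits.** The wording allows this but does not establish it.
- **That extra contact explains a particular share of the expected difference.** The article gives no effect of contact, so no size can be put on it.

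The point should be corrected because it governs what the trial may claim. It does not threaten the validity of the comparison.

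**What to change.** 1. In the Abstract, Introduction and Conclusions, restate the aim as the add-on effect of an exercise-prescription package (exercise plus its supportive contact) in smokers receiving cytisinicline and brief advice, in line with sections 3 and 4.
2. In section 2.14, limit identical monitoring to the scheduled visits and outcome measurements, and declare the additional contact part of the experimental intervention.
3. In section 2.12, state that motivation to continue exercise applies to the experimental arm only. Keep recording exercise in both arms, so that uptake among controls can be seen.
4. Record the number of contacts for each participant and report it by arm.

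No new arm and no larger sample are needed. The costs are a narrower claim, a contact count in the data collection, and an amendment with prior ethics authorisation, which section 2.18 requires. The results will still not separate exercise from its supportive contact, and the report should say so.
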